## Abstract

**Introduction:**

The predisposition to food allergy development and the induction of allergen-specific immune responses appears to be initiated early in infancy. Early exposure to food allergens, such as peanut and cashew nut, via human milk is likely important in initiating oral tolerance and reducing risk of food allergy development. This trial aims to determine if the risk of developing peanut and cashew nut allergy during infancy can be reduced by a high peanut and cashew nut maternal diet during lactation.

**Methods and analysis:**

This is a multisite, parallel, two-arm (1:1 allocation), single-blinded (outcome assessors, statistical analyst and investigators), randomised controlled trial. Target sample size is 4412 participants (2206 per group). Women (aged 18–50 years) with a singleton pregnancy, who are planning to breastfeed and do not have peanut and/or cashew nut allergies are eligible to participate. After obtaining written informed consent, participants are randomised to either a high peanut and cashew nut diet (at least 60 peanuts and 40 cashew nuts per week) or a low peanut and cashew nut diet (no more than 20 peanuts and 12 cashew nuts per week). Participants are asked to follow their allocated diet from birth to 6 months postnatal. Individual lactation consultant advice and support is provided as required. The study’s primary outcome is food challenge proven IgE-mediated peanut and/or cashew nut allergy during infancy (0–18 months). Key secondary outcomes include infant sensitisation to peanut and/or cashew nut. Analyses will be performed on an intention-to-treat basis according to a prespecified statistical analysis plan.

**Ethics and dissemination:**

Ethical approval has been granted from the Western Australian Child and Adolescent Health Service Human Research Ethics Committee (approval number RGS0000006685). Trial results will be presented at scientific conferences and published in peer-reviewed journals.

**Trial registration number:**

Australian New Zealand Clinical Trials Registry (ACTRN ACTRN12624000134527)

Strengths and limitations of this studyThis study is a large randomised controlled trial designed with adequate power to assess the effect of higher maternal peanut and cashew nut consumption during the first 6 months of lactation on infant peanut and cashew nut allergy outcomes.The provision of individual participant advice and support by an international board-certified lactation consultant to establish and maintain breastfeeding will enhance breastfeeding rates until at least 6 months postnatal.The use of peanuts, peanut butter, cashew nuts and cashew nut spread for the maternal intervention, rather than powders or specific products, will enable rapid low-cost direct translation into practice recommendations.This study is single-blinded due to the use of peanuts, peanut butter, cashew nuts and cashew nut spread for the intervention; however, the outcome assessors, statistical analyst and investigators are all blinded to intervention group allocation.

## Introduction

 Overall, peanut allergy prevalence is reported to be between 1% and 2% in the Western nations.^1^ In Australia, 3.1% of infants develop peanut allergy^2^ and 1.5% develop cashew nut allergy.^3^ The Learning Early about Peanut Allergy (LEAP) randomised controlled trial demonstrated that regular inclusion of peanut-containing foods from solid food introduction until 5 years of age, compared with peanut avoidance, reduces the risk of peanut allergy at 5 years of age (1.9% consumption group compared with 13.7% avoidance group, p<0.001).^4^ However, the effect of regular peanut consumption in early childhood was found to be peanut allergen-specific and did not reduce allergic reactions to other foods, such as tree nuts.^5^ Importantly, 76/834 (9.1%) of infants initially screened for the LEAP trial were excluded from participation due to already having peanut sensitisation (peanut skin prick test of >4 mm) prior to dietary peanut exposure,^4^ while another 7 had allergic reactions on their first peanut ingestion at the baseline peanut challenge.^4^ Consistent with these findings, we have demonstrated that some infants have allergic reactions, including anaphylaxis, on first known introduction of egg as early as 4 months of age,^6^ and that these infants have in vitro egg allergen-specific immune responses established at this age.^7^ Furthermore, these immune responses were not altered by early introduction of egg in the infant diet.^7^ Hence, it may be too late for timely allergenic foods introduction in the infant’s diet to change the trajectory for some susceptible infants who are already sensitised/allergic by that age. Thus, intervention strategies are needed earlier in life when the pathways to food allergy development appear to be initiated.

Peanut proteins have been detected in human milk^8^,^11^ and may be important early sources of oral peanut exposure. In animal studies, peanut exposure via maternal milk has been shown to induce oral tolerance.^8^ These tolerogenic effects are assisted by allergen-antibody complexes, which induce allergen-specific T regulatory cells in newborn animals^12 13^ and are also present in human milk.^14^ We have shown that the amount of egg eaten in the maternal diet during lactation influences egg protein concentration in human milk,^15^ and that infant egg-specific antibody blood concentrations are positively associated with maternal egg ingestion during early lactation.^16^ This is consistent with findings that maternal cow’s milk avoidance is associated with lower infant cow’s milk-specific antibody blood concentrations and increased risk of infant cow’s milk allergy.^17^ Hence, we propose that higher maternal consumption of nuts during lactation would increase early infant oral nut exposure in association with tolerogenic nut-specific antibody complexes in human milk.

There is currently insufficient evidence to inform maternal diet recommendations for prevention of food allergy and global allergy prevention guidelines do not provide any advice in this regard. Based on a lack of high-quality evidence, an international expert review concluded that maternal peanut ingestion during breastfeeding, in combination with infant ingestion of peanut, might have a role in peanut allergy prevention, although further studies are required.^18^ We completed a pilot randomised controlled trial^19^ of 109 infants at high risk of developing food allergy (≥2 immediate family members with history of allergic disease). This pilot trial was designed primarily to determine feasibility and compliance with the maternal dietary interventions for the first 6 months of lactation. The pilot trial was not designed with adequate power to determine differences in infant clinical outcomes between the maternal intervention diet groups. In this pilot, we discovered that a maternal high-peanut diet, compared with a low-peanut diet, during the first 6 months of lactation may reduce the risk of infant peanut allergy development. No infants developed peanut allergy after their mothers consumed a high-peanut diet, compared with 8.2% of infants whose mothers followed a low-peanut diet. Consistently, only 2.3% of infants in the maternal high-peanut diet group were sensitised to peanut, compared with 15.2% of infants in the low-peanut group.

Our hypothesis generated from current evidence is that higher maternal peanut and cashew nut consumption during lactation may reduce the development of infant peanut and cashew nut allergies. Thus, we aim to investigate in a randomised controlled trial the effectiveness of higher regular peanut and cashew nut maternal dietary intakes during the first 6 months of lactation as a strategy to prevent peanut and cashew nut allergies in infants.

## Methods and analysis

### Trial design and study setting

This is a multisite, parallel, two-arm (1:1 allocation), single-blinded (outcome assessors, statistical analyst and investigators), randomised controlled trial, known as the Nuts For Babies Study.

### Recruitment

Trial participant flow is illustrated in figure 1. Participant recruitment will occur in the Australian states of Western Australia and Victoria using online (via social media advertising) and in-person (at maternity hospital antenatal clinics/classes) strategies. After screening to ensure inclusion and exclusion criteria are met, a participant information and consent form describing the purpose of the study, the procedures to be followed and the risks and benefits of participation is provided to interested participants. Potential participants are given as much time as they wish to consider participation in the study, have any questions answered or to discuss taking part with their family, friends and/or healthcare professionals. Participants are required to provide written informed consent and are given a copy of their signed consent form. A record of all potential participants screened and their enrolment status is maintained to adhere to the Consolidated Standards of Reporting Trials (CONSORT).^20^ Participants may withdraw their involvement in the trial at any time, without explanation and without prejudice to their future care. Wherever possible, the reason for withdrawal will be recorded. Participants who discontinue or are withdrawn will not be replaced.

**Figure 1 F1:**
[figure not shown]
Trial participant flow diagram.

### Participant eligibility criteria

The inclusion criteria are women (aged 18–50 years) able to give informed consent, with a singleton pregnancy, who are planning to breastfeed. The exclusion criteria are women with peanut and/or cashew nut allergies, as they would be unable to safely follow the intervention without allergic reactions, and participants who have already participated in this Nuts For Babies Study with a previous child.

### Allocation of interventions

After confirming eligibility, participants provide written informed consent prior to trial randomisation. Trial intervention team research staff use a secure web-based randomisation service embedded within the secure trial-specific Research Electronic Data Capture (REDCap) database. The randomisation service allocates a unique uninformative participant trial identification number and a group allocation according to a computer-generated randomisation schedule, produced by a statistician not otherwise involved in the trial. Randomisation is stratified by state (Western Australia or Victoria), and by any parental/sibling (of the infant) history of eczema/atopic dermatitis or IgE-mediated food allergy,^21^ using randomly permuted blocks of varying sizes. Block sizes will not be disclosed to ensure allocation concealment. Following randomisation, intervention phase research staff explain the participant’s intervention allocation via a telephone call.

### Blinding

Due to the nature of this type of dietary intervention, it is not possible to blind the participants or intervention phase research staff responsible for providing dietary advice and undertaking all participant contact phone calls during the intervention period. However, research staff undertaking the outcome assessments, all investigators and statistical analysts are blinded to intervention allocation. At each contact phone call or appointment, outcome assessors remind participants not to disclose their diet group allocation.

### Interventions

The participants are randomised to either a high peanut and cashew nut diet (intervention) group or a low peanut and cashew nut diet (control) group.

#### High peanut and cashew nut diet (intervention) group

Maternal consumption of at least 60 peanuts and 40 cashew nuts per week from birth until 6 months postnatal.

#### Low peanut and cashew nut diet (control) group

Maternal consumption of no more than 20 peanuts and 12 cashew nuts per week from birth until 6 months postnatal.

The Australian Bureau of Statistics Australian Health survey data found that, on average, Australians consume around 32 g per week of any nuts. This includes peanuts and cashew nuts. Our low nut diet (control) group reflects this with no more than 20 peanuts (approximately 18 g) and no more than 12 cashew nuts (approximately 22 g) per week, thus in total no more than 40 g per week.

Weekly nut ingestion targets can include peanuts and/or peanut butter, and cashew nuts and/or cashew nut spread. To assist with diet compliance a fridge magnet specific to intervention group allocation is provided to each participant including nut conversion details (eg, five peanuts=one teaspoon (5 mL) of peanut butter, four cashew nuts=one teaspoon of cashew nut spread). Participants are encouraged to contact the intervention phase research staff at any stage during the intervention period if they require further dietary adherence assistance.

The dosages of peanut consumption for each group have been matched to those used in the pilot trial,^19^ where 80% compliance was achieved by both allocated groups. The doses in the pilot trial were based on another trial,^16^ where we determined that for each additional egg eaten per week, there was an average 25% increase in egg protein (ovalbumin) breast milk concentration and 22% increase in infant egg-specific IgG4 concentrations (associated with tolerance development). Peanut protein (Ara h 6) has been detected in breast milk samples at similar concentrations to the egg protein (ovalbumin) after 30 g peanuts and one egg ingestion, respectively. Hence, the quantities of peanut chosen for the maternal high-peanut intervention group of at least 60 peanuts eaten per week should induce beneficial infant peanut-specific immune responses in early postnatal life. Maternal consumption of at least 60 peanuts per week in the intervention group is projected to result in a threefold increase in infant peanut-specific IgG4 concentrations above those of the control group (maternal consumption of no more than 20 peanuts per week). The cashew nut quantities are matched for equivalent protein content.

The control group women will be recommended to eat other tree nuts (eg, almonds) as snack suggestions to provide good nutritional sources of energy, protein, fibre, magnesium, B group and E vitamins, as these are also good nutritional sources from peanut and cashew nut consumption. Other tree nuts, such as almonds and hazelnuts, have different nut-specific allergens to those found in peanuts and cashew nuts.

Participants who cease breastfeeding prior to 6 months will remain in the trial and will be asked to continue their allocated peanut and cashew nut diet until their infant is 6 months of age. This is important to continue the consistency of maternalinfant environmental peanut and cashew nut exposure concentrations as would be the usual ‘real-life’ scenario where women would not usually change their diet when they cease breastfeeding. All infants will participate in the follow-up period regardless of duration of breastfeeding or maternal peanut and cashew nut intervention group adherence. Research staff at each site who provide the dietary group allocation advice to participants are trained by the intervention team clinical trial coordinator, and the research staff’s intervention advice is monitored on a 6 monthly basis throughout the trial.

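### The nut weights and the teaspoon conversion for spreads do not fit together, so either the stated cashew weight or the conversion given to participants needs correcting

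*Protocol article*

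**What the plan says.** All the figures are in the Interventions section of the protocol article.

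- The high-diet target is "Maternal consumption of at least 60 peanuts and 40 cashew nuts per week from birth until 6 months postnatal". The control ceiling is "Maternal consumption of no more than 20 peanuts and 12 cashew nuts per week from birth until 6 months postnatal".
- The control ceiling is also given by weight: "no more than 20 peanuts (approximately 18 g) and no more than 12 cashew nuts (approximately 22 g) per week". This is summed to 40 g and compared with a national average of around 32 g of nuts per week.
- Either form counts: "Weekly nut ingestion targets can include peanuts and/or peanut butter, and cashew nuts and/or cashew nut spread".
- To help with compliance, "a fridge magnet specific to intervention group allocation is provided to each participant including nut conversion details". The example given is "five peanuts=one teaspoon (5 mL) of peanut butter, four cashew nuts=one teaspoon of cashew nut spread".
- On the choice of amounts: "The cashew nut quantities are matched for equivalent protein content".

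Under Intervention compliance, adherence is monitored by a fortnightly self-report of the peanut and cashew eaten in the past week. Under Data analysis plan, adherence to the allocated intakes, together with breastfeeding to 6 months, defines a supplementary per-protocol analysis. The primary analysis is by intention to treat.

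**The concern.** The weights make a cashew about twice as heavy as a peanut, yet the conversion puts nearly as many cashews as peanuts into one teaspoon. The same spoon is therefore credited with very different masses of nut.

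This is more than a clerical matter, because the conversion is how a mother who eats spread works out whether she has met her target. If it does not agree with the whole-nut amounts, two mothers credited with the same weekly intake may have eaten different amounts, depending on the form they chose. The adherence record and the per-protocol set would inherit the difference. If instead the cashew weight is the figure at fault, what suffers is the argument that the control diet reflects ordinary national intake.

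**Working it through.** Inputs from the Interventions section: 20 peanuts ≈ 18 g; 12 cashews ≈ 22 g; 5 peanuts or 4 cashews per teaspoon; teaspoon = 5 mL (written for peanut butter, taken to apply to both); high-diet targets of 60 peanuts and 40 cashews. Assumed, not in the documents: the two spreads have similar density, in the range 0.9 to 1.2 g/mL, and are all nut.

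1. The plan's own total: 18 + 22 = 40 g. Reproduced.
2. Weight per nut: 18/20 = 0.90 g per peanut; 22/12 = 1.83 g per cashew.
3. Nut credited per teaspoon: 5 × 0.90 = 4.5 g of peanut; 4 × 1.833 = 7.33 g of cashew. Ratio 7.33/4.5 = 1.63. Over 5 mL these are 0.90 and 1.47 g/mL.
4. Rounding: taking 18 g as 17.5 to 18.5 and 22 g as 21.5 to 22.5, the ratio runs from 7.17/4.625 = 1.55 to 7.50/4.375 = 1.71. Rounding does not close the gap.
5. If the conversion stands and the cashew weight is wrong: a teaspoon holds 5 × 0.9 to 5 × 1.2 = 4.5 to 6.0 g, so a cashew weighs 1.13 to 1.50 g and 12 cashews weigh 13.5 to 18 g. With 18 g of peanut, the control ceiling is 31.5 to 36 g, not 40 g.
6. If the weights stand and the conversion is wrong: 40 cashews = 40 × 1.833 = 73.3 g, and 40/4 = 10 teaspoons = 50 mL. For peanut, 60 × 0.90 = 54 g, and 60/5 = 12 teaspoons = 60 mL.

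| Assumed density (g/mL) | 10 tsp cashew spread | vs 73.3 g | 12 tsp peanut butter | vs 54 g |
|---|---|---|---|---|
| 0.9 | 45 g | −39% | 54 g | 0% |
| 1.0 | 50 g | −32% | 60 g | +11% |
| 1.1 | 55 g | −25% | 66 g | +22% |
| 1.2 | 60 g | −18% | 72 g | +33% |

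The cashew gap closes only at 1.47 g/mL. There a teaspoon of peanut butter would hold 7.33 g, 63% above its credited 4.5 g.

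7. Protein matching: with the stated weights, matching implies that cashew has 54/73.3 = 0.74 (high diet) to 18/22 = 0.82 (control diet) of peanut's protein per gram. Under the conversion at equal density, matching implies 12/10 = 1.20 (high diet) to 4/3 = 1.33 (control diet). One reading makes cashew poorer in protein than peanut per gram, the other richer. The documents give no protein content, so they do not settle it.
8. Contrast between arms for cashew: whole nuts in both arms, 40/12 = 3.33-fold; spread in both arms, 10/3 = 3.33-fold. If the weights stand, the high arm uses only spread to target and the control arm eats whole cashews to its ceiling, it is 45/22 to 60/22 = 2.0- to 2.7-fold.

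**The case against.** The weights are marked as approximate, the conversion is an example from a magnet that is not shown, 5 mL is written only for peanut butter, and no spread density is given. A heaped spoon could make up part of a shortfall. These points are fair, and they make the size uncertain. They do not make the two lines agree: rounding leaves at least a 1.55-fold gap, and both lines use the same unit.

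A reader might infer that mothers using spread are in fact under-exposed to cashew. The documents do not support that as fact. The targets are set in numbers of nuts, so if the 22 g figure is the error, spread and whole nuts can agree and nobody is under-dosed by using spread. The corrected control total of 31.5 to 36 g would even lie closer to the national 32 g.

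A reader might also set 60:40 (1.50), 20:12 (1.67) and 12:10 teaspoons (1.20) side by side as three conflicting matches. That does not stand. The teaspoon counts were never said to be matched, and the difference between 1.50 and 1.67 is explained by practical rounding: one third of 40 is 13.3, against a ceiling of 12.

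Finally, a reader might infer that a null cashew result could not be told apart from under-exposure. That is unsupported. Both arms get the same conversion, the contrast stays at about 2.0-fold or more in every case computed, and adherence enters only the supplementary analysis. That a spread user would be credited with meeting the target is itself inferred from the conversion, since the article shows no adherence formula.

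**Conclusion.** The point holds as an internal inconsistency. On the article's own figures, one teaspoon is credited with 1.63 times as much cashew as peanut (1.55 to 1.71), which cannot be right for both if the spreads have similar density. The documents do not show whether the cashew weight or the conversion is at fault.

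The consequence depends on which. If it is the weight, the 40 g ceiling and its comparison with national intake are wrong, and exposure is not affected. If it is the conversion, meeting the cashew target with spread alone gives 18% to 39% less cashew than meeting it with whole nuts, on assumed densities of 0.9 to 1.2 g/mL. The share of mothers using spread is not known, so the average effect cannot be sized. The reach is limited to the description of the diets, adherence and the supplementary per-protocol set. The intention-to-treat primary analysis is unaffected, as is the sample size, which rests on the 3.1% prevalence reported for peanut allergy.

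**What to change.** Reconcile the nut weights, the protein-matching statement and the teaspoon conversion in the Interventions section, and correct whichever figure is wrong. This review does not say which. Product labels (grams per teaspoon, protein per gram) should help, since the two readings imply opposite orderings of protein content. If the conversion is the part that changes, the magnet needs the same correction.

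Then apply one verified nut and spread conversion, in grams or protein, to the reported intakes when adherence and the per-protocol set are defined. Use separate entries for whole nuts and spread where the survey records them. The article does not show the survey items, so separate recording may already be in place; if not, it is a small change to the survey.

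The cost is a label check, one conversion table and possibly that survey change. The downside is that some adherence classifications may change, and surveys already collected may not separate the two forms. With recruitment expected to run to December 2027, a correction made soon would still reach participants yet to be enrolled.

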### Intervention compliance

To monitor intervention adherence, every 2 weeks during the intervention period, the participants are sent a mobile phone text with a link to complete a short survey about how much peanut and cashew nut they consumed over the past week, and whether they would like any further advice and support regarding their allocated nut diet. This survey also assesses current breastfeeding status and whether the participants would like to be referred to an international board-certified lactation consultant for any advice and support. For the promotion of breastfeeding, an international board-certified lactation consultant can assist and provide advice to the participants with establishing and maintaining breastfeeding until at least 6 months postnatal.

